## Abstract

**Background:**

Intensive care units (ICUs) present a highly stressful environment for patients, relatives, and health care professionals, often resulting in psychological distress. Despite the well-documented psychosocial burden, there is a lack of low-threshold, integrated support structures for all target groups. Based on the findings of phase A, a complex intervention was developed involving the permanent integration of study therapists into ICU teams.

**Objective:**

This pilot study (phase B of the Integrated Psychosocial Care [IPS]-Pilot project) aims to assess the feasibility of a pragmatic, cluster–randomized controlled trial (pilot RCT) to evaluate the implementation, acceptability, and potential impact of an integrated psychosocial intervention in adult ICU settings.

**Methods:**

A multicenter, cluster-randomized feasibility trial is conducted across 8 ICUs in Germany (Ulm, Berlin, and Magdeburg). The intervention group received continuous support from study therapists embedded within the ICU team. The control group continues with usual psychosocial care (eg, consultation-based). Mixed methods are applied: quantitative surveys at 2 time points (baseline and follow-up) for health care professionals and relatives, and 1-time follow-up for patients; qualitative interviews with study therapists and health care professionals after 4 months. Additional continuous documentation of the intervention process is conducted by study therapists. Data collection was pseudonymized and managed via secure, General Data Protection Regulation–compliant infrastructure.

**Results:**

Funding for the IPS-Pilot project was awarded in January 2023. Recruitment and baseline data collection for phase B began in July 2024 and were ongoing at the time of manuscript submission (May 2025). By March 2025, 177 health care professionals and 82 relatives had completed baseline questionnaires. In addition, all planned qualitative process interviews with all 4 study therapists and 22 health care professionals were conducted in month 4 of the intervention. Data collection took place through June 2025. The initial study results are scheduled to be published in 2026, following the completion of data analysis.

**Conclusions:**

Preliminary findings suggest that the intervention may be feasible and well accepted. The study design enables the identification of contextual barriers and facilitators, informing the development of a future effectiveness trial. Methodological triangulation ensures robust insights into real-world implementation challenges. Final results will contribute to the design of a subsequent definitive trial.

## Introduction

### Background

Intensive care units (ICUs) are characterized by a high level of psychosocial stress, which represents a considerable challenge for patients, relatives, and health care professionals. This burden manifests in anxiety, stress reactions, and other psychological symptoms and can affect both the quality of life of those affected and the quality of medical care. Patients in ICUs often experience anxiety, delirium, and posttraumatic stress. Postintensive care syndrome describes the long-term physical, psychological, and cognitive consequences of an intensive care stay and affects up to 50% of survivors [1,2]. Relatives are also often under considerable strain: concern about the state of health, uncertainty in medical decisions, and emotional overload can lead to symptoms of anxiety disorders, acute stress reactions, or posttraumatic stress disorder [3]. Health care professionals are also severely affected: time pressure, difficult ethical decisions, and constant confrontation with serious illnesses increase the risk of mental illnesses such as burnout, depressive symptoms, and secondary traumatization [4].

During the COVID-19 pandemic, psychosocial support services for health care professionals were temporarily introduced in many hospitals. However, these measures were mostly temporary and not sustainably integrated into everyday hospital life [5,6]. Although the psychosocial burden in ICUs is well documented [7], there is still a lack of standardized and permanently integrated support structures that address all 3 affected groups—patients, relatives, and health care professionals—together [8,9].

### Relation to Phase A

In phase A of the IPS-Pilot project, the psychosocial needs of patients, relatives, and health care professionals in intensive care were systematically surveyed using qualitative interviews, focus groups, and a quantitative survey [10,11]. The focus was not on the direct survey of stress experiences but on the analysis of support needs, as well as hindering and supporting factors for psychosocial care. The following key challenges were identified: (1) lack of continuous psychosocial support for all target groups, (2) insufficient communication and decision support, and (3) high psychological strain on health care professionals without structural relief programs [10].

Based on these results, a complex psychosocial intervention was developed that includes a psychologist as a permanent team member in the ICU. The development was guided by theory (including the conservation of resources theory [12], psychosocial safety climate [13], and the Medical Research Council [MRC] framework [14]) and was carried out in a participatory manner involving all groups involved.

### Necessity of the Feasibility Study

Complex psychosocial interventions in the context of intensive care medicine are associated with numerous practical, organizational, and ethical challenges. Systematic reviews show that existing interventions usually address only 1 target group, while integrated approaches have hardly been systematically investigated to date. At the same time, the implementation of randomized studies in ICUs is difficult—due to the high heterogeneity of patients, ethical concerns, and logistical hurdles, among other things [15-17].

The UK MRC framework for complex interventions, therefore, explicitly recommends an upstream feasibility study before a large-scale effectiveness trial can take place [14]. Phase B of the Integrated Psychosocial Care (IPS)-Pilot project takes up this recommendation and uses a pilot randomized controlled trial (RCT) to test whether the planned intervention can be implemented under realistic conditions and how a subsequent effectiveness design might need to be adapted.

### Objectives

The aim of this pilot study is to test the feasibility of an RCT to evaluate a complex psychosocial intervention in an intensive care context. The study follows the framework for complex interventions outlined by MRC and does not focus on proof of effectiveness, but rather on the practical feasibility of the planned procedures related to both the intervention and pilot RCT.

The objectives include (1) the examination of the recruitability of patients, relatives, and health care professionals; (2) the analysis of the acceptance and perceived usefulness of the intervention; (3) the evaluation of the integration of the intervention into existing clinical processes; (4) the documentation of adherence to the intervention; and (5) the identification of barriers and conditions for success for a subsequent main study.

### Research Questions

The primary research question is “Is a pragmatic RCT to evaluate the IPS-ICU intervention feasible in terms of recruitment, randomization, implementation, and follow-up?”

The secondary research questions are as follows:

Is the intervention practicable and realizable in the daily clinical routine of an ICU?How is the intervention perceived by patients, relatives, and health care professionals?What structural, organizational, and logistical challenges are involved in implementation?To what extent can the intervention be integrated into existing workflows and team structures in the ICU?Is there initial evidence that the intervention has positive effects on the psychosocial safety climate and the well-being of those involved?

## Methods

### Study Design

The reporting of the methodological procedures follows the CONSORT (Consolidated Standards of Reporting Trials) extension for feasibility studies (Checklist 1) [18].

This multicenter, cluster-randomized, controlled feasibility study is being conducted in 8 general ICUs for adults at 3 sites in Germany (Ulm, Magdeburg, and Berlin). The 8 participating wards were determined in advance and selected according to practical criteria, such as minimum capacity, logistical feasibility, and approval from hospital management. Allocation to the intervention or control group was carried out in a 1:1 ratio at the cluster level (ICU) using computer-assisted randomization via the Randomizer tool (Medical University of Graz) [19]. Randomization was performed by the central study coordinator at Ulm University Hospital. Allocation was concealed at the cluster level through the use of a centralized, computer-based randomization procedure. As randomization was conducted at the ICU level prior to participant inclusion, allocation concealment at the individual participant level was not applicable. Both groups receive psychosocial care—either through the established counseling services or via the implemented study therapist.

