### Blinding and Risk of Contamination

Patients, relatives, and health care professional participants are not explicitly informed about ward allocation in the study information materials. It was not specified whether the respondents were on an intervention or control ward. Health care professionals are not actively informed about the group assignment either. However, as a psychologist is permanently integrated into the team on intervention wards, group assignment can still be inferred based on the care structure. The project management, ward management, and the study therapist were informed about the group assignment; further communication of the assignment was avoided. Full blinding of health care professionals to group allocation is not feasible in this trial because the permanent integration of a study therapist on intervention wards is visible in daily practice. By contrast, patients and relatives are not explicitly informed about the intervention content or their group assignment. In the informed consent materials, all participating wards are described as providing psychosocial care, and the study is presented as an investigation of emotional health during and after intensive care. Because most patients receive treatment on only one ICU ward and transfers between participating ICUs are rare, they have no direct comparison standard and are therefore unlikely to distinguish intervention from usual care conditions.

To minimize contamination at the organizational level, study therapists are exclusively assigned to intervention wards and do not provide structured psychosocial counseling on control wards. Existing consultation-liaison services on control wards continue unchanged, without additional involvement from the IPS-Pilot team. Any observations deviating from our expectations will be documented via the process documentation.

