### Pilot Effectiveness Evaluation

#### Overview

Although the intervention and its evaluation are closely linked, they represent 2 methodologically distinct components of the project. The intervention involves the permanent integration of clinical study therapists into the intensive care team.

The accompanying study systematically evaluates the feasibility of conducting an RCT to evaluate the intervention. Key criteria for the feasibility of the RCT include participation and dropout rates, data completeness, and the overall practicability of the administered questionnaire. The feasibility of the intervention is assessed in terms of participation, dropout rates, fidelity, and acceptance. Both quantitative and qualitative methods are applied.

The study is aimed at 3 groups in intensive care: patients, their relatives, and health care professionals.

Planned sample sizes are (1) up to 125 patients and their relatives during the course of the study, and (2) approximately 250 health care professionals. The planned sample size is based on feasibility considerations rather than a formal statistical power calculation. In line with recommendations for pilot and feasibility trials, the sample is intended to provide sufficient information on recruitment processes, data completeness, and variability of candidate outcome measures to inform the design of a subsequent definitive trial.

The standardized survey is conducted with health care professionals at 2 measurement points: a baseline survey (*t*_0_), which is administered within 6 weeks of the start of the intervention for health care professionals and a second survey (*t*_1_) at the end of the intervention phase. Relatives and patients are recruited during the patient’s ICU stay; however, only for relatives, a baseline survey (*t*_0_) is administered during that time to avoid placing a high burden on patients. The follow-up survey (*t*_1_) is conducted with relatives and patients 4 months after discharge from the ICU.

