The selection of multiple psychosocial outcomes reflects the complex and multilevel nature of psychosocial burden in the ICU context, which affects individual well-being, symptoms of anxiety and depression, perceived stress, and team processes among health care professionals. Combining generic well-being and health-related quality of life measures (World Health Organization–Five Well-Being Index [WHO-5] and 12-Item Short Form Health Survey [SF-12]) with brief symptom scales (Patient Health Questionnaire–4 [PHQ-4] and Perceived Stress Scale–10 [PSS-10]) and work-related constructs (psychosocial safety climate, team cohesion, and irritation) allows us to capture different, theoretically grounded dimensions that may respond differentially to the intervention [12,13,20-28]. In line with recommendations for feasibility studies of complex interventions [14,18], this broad set of candidate outcomes will be used to evaluate acceptability, completeness, and distributional properties, and to inform the selection of a smaller number of primary and key secondary endpoints for a future definitive trial. The aim was an economical but, at the same time, differentiated survey of psychosocial stress and well-being dimensions, which could also be considered relevant target variables for a later main study. Given the feasibility focus of this pilot trial, all analyses will be primarily descriptive. Feasibility outcomes (eg, participation rates, drop-out rates, and data completeness) will be summarized using absolute and relative frequencies, as well as means with SDs or medians with IQRs, as appropriate. No formal hypothesis testing or confirmatory effectiveness analyses are planned. Exploratory analyses of candidate outcome measures will be conducted to assess distributional properties and missingness, with the aim of informing endpoint selection for a subsequent definitive trial.

The following questionnaires are used for health care professionals: WHO-5 [20], Psychosocial Safety Climate Questionnaire [21], Questionnaire for Self-Efficacy, Optimism, and Pessimism [22], SF-12 [23], PSS-10 [24], PHQ-4 [25], Erlangen Team Cohesion at Work Scale (validated German version) [16], Irritation Scale for work-related stress consequences [27], and Intention to Leave (items from the NEXT-study) [29]. For patients and relatives, the following questionnaires are used: WHO-5 [20], SF-12 [23], PSS-10 [24], and PHQ-4 [25].

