#### Data Completeness

Another important criterion is the completeness of data collection. For each target group and survey time point, the proportion of missing data will be monitored and reported. Acceptable thresholds are 20% or less missing data for core outcome variables [38].

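### The question about initial evidence of effects has no stated analysis, and the progression limits are set per stakeholder group only, so a decision to proceed could hide differences between arms in a trial that recruits after ward allocation

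*Protocol article*

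**What the plan says.** All places are in the protocol article.

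- **Effects.** Research Questions includes "Is there initial evidence that the intervention has positive effects on the psychosocial safety climate and the well-being of those involved". Inclusion and Exclusion Criteria repeats an aim of assessing the intervention's possible effects from the viewpoint of all three groups.
- **Analysis.** Measures calls the analyses mainly descriptive and excludes hypothesis tests and confirmatory effectiveness analyses. It gives the exploratory analyses of candidate outcomes one purpose: to look at distributions and missing values so that endpoints can be chosen for the later trial. For feasibility it says "Feasibility outcomes (eg, participation rates, drop-out rates, and data completeness) will be summarized using absolute and relative frequencies".
- **Unit of reporting and decision.** Data Completeness says "For each target group and survey time point, the proportion of missing data will be monitored and reported". The traffic-light rule in Feasibility Evaluation refers to stakeholder groups. Target Participation Rates relates participation to overall planned numbers (about 250 professionals, 125 patients and relatives). None of these names arm or ward.
- **Design.** The study "is being conducted in 8 general ICUs for adults at 3 sites in Germany", with wards allocated 1:1. Study Design adds "As randomization was conducted at the ICU level prior to participant inclusion, allocation concealment at the individual participant level was not applicable". On who knew the allocation, Blinding and Risk of Contamination says "The project management, ward management, and the study therapist were informed about the group assignment; further communication of the assignment was avoided". The same section grants that staff can see the therapist at work.

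**The concern.** There are two linked gaps.

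First, a question about effects needs a contrast between arms, and the purpose given for the outcome analyses does not lead to one. If the authors follow the text, the question goes unanswered. If they answer it anyway, the estimate is chosen after the data are in, and nothing obliges them to show how imprecise eight wards make it.

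Second, when wards are allocated before individuals are approached, knowledge of the arm can influence who is invited, who agrees and who stays. That is a reason to look at recruitment by arm, and calling individual-level concealment not applicable passes over it. Professionals are exposed too: their baseline survey falls in the first six weeks of the intervention, when a therapist is already on the intervention wards. The primary research question is whether a randomised trial is feasible, including its recruitment and follow-up. A rule applied to whole stakeholder groups can return a decision to proceed while one arm recruits or retains poorly.

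**Working it through.** The article gives no power calculation, SD or ICC, so there is no stated figure to reproduce. What follows is illustration.

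**1. What a group-level figure can hide.** Assume equal denominators per arm, so that the pooled rate is the mean of the two arm rates.

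- Missing data, limit 20% to proceed and above 30% not to proceed: (8 + 32)/2 = 20. The group meets the first limit while one arm is beyond the second.
- Dropout, limit 35%: (20 + 50)/2 = 35. The group meets the limit while one arm loses half.
- Participation, 80% to proceed: (95 + 65)/2 = 80.
- Counts in Results: professionals 177/250 = 70.8%. If half of the 250 were planned per arm (125) and one arm reached 90%, the other would be at (177 − 112.5)/125 = 51.6%. Relatives: 82/125 = 65.6%. With 62.5 per arm and one arm at 90%, the other would be at (82 − 56.25)/62.5 = 41.2%.

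These splits are possible, not observed. The article gives no counts by arm and no planned number per arm.

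**2. Precision of an arm difference.** Inputs: 8 wards at 1:1, so 4 per arm; m = 177/8 ≈ 22 professionals per ward; ICC of 0.02 to 0.10 (assumed); equal ward sizes; no site effect. Degrees of freedom are 8 − 2 = 6, with t(0.975, 6) = 2.447.

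Half-width in SD units = t × √[2(1 + (m − 1)ICC)/(4m)]

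- ICC 0.02: 2.447 × √(2 × 1.42/88) = 0.44
- ICC 0.05: 2.447 × √(2 × 2.05/88) = 0.53
- ICC 0.10: 2.447 × √(2 × 3.10/88) = 0.65

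**3. Precision of a group-level rate.** Take 80% on 250 people. Ignoring wards, 1.96 × √(0.8 × 0.2/250) = 5.0 points. With 250/8 = 31.25 per ward, design effect D = 1 + 30.25 × ICC, and t(0.975, 7) = 2.365, the half-width is 2.365 × √(0.00064 × D):

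- ICC 0.02, D = 1.605: 7.6 points
- ICC 0.05, D = 2.51: 9.5 points
- ICC 0.10, D = 4.03: 12.0 points

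Rates by arm would be less precise still, so by-arm figures can describe a gap but cannot support a sharp cut-off on its size.

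**The case against.** The strongest reply is that the article is silent rather than wrong. It plans descriptive analyses, excludes only tests and confirmatory analyses, and never says that arms will be pooled. Table layouts, cluster-adjusted intervals and ICCs are normal content for a full protocol or analysis plan that is not shown. This stands in part. A reader might infer that the plan cannot show differential recruitment. It can, because ward and arm are known by design; the article just does not commit to showing it. The absence of an ICC table is likewise no finding.

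A reader might also infer that the plan promises between-ward variance. It does not: the sample-size text speaks of "variability of candidate outcome measures to inform the design of a subsequent definitive trial" and mentions neither that variance nor an ICC. Nor does the article say that candidate outcomes will be summarised by SDs that ignore the ward. The SDs appear in the sentence on feasibility outcomes.

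The blinding section offers safeguards. Patients and relatives are not told their allocation, consent materials describe all wards alike, and unexpected observations are documented. These reduce selection by patients and relatives. They do not cover staff, who can infer the arm when deciding whether to respond, and the article does not say who approaches patients and relatives.

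Finally, participation is measured against overall targets with no denominator per arm, so the participation threshold cannot simply be applied to each arm. That stands, and the fix allows for it.

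Two things survive: the stated purpose of the outcome analyses does not match the effects question, and the progression rule is fixed at a level that does not register arm imbalance.

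**Conclusion.** The concern holds in limited form. The article asks about effects and states no analysis that would answer the question. This touches one secondary question in a study that disclaims proof of effectiveness. Its progression and completeness rules work at stakeholder-group level although inclusion follows a ward allocation known to some and visible to staff, so a decision to proceed is compatible with a marked difference between arms. Nothing in the document shows that such a difference has occurred.

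On size, the group-level limits can coexist with arm gaps of 24 points in missing data (8 against 32) and 30 points in dropout (20 against 50), assuming equal arms. Any arm difference in an outcome among professionals would be known only to about ±0.44 to ±0.65 SD, assuming 22 per ward, equal wards and ICCs of 0.02 to 0.10. Such estimates can be reported but can support no more than description.

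**What to change.** 1. **Effects question.** Either state in Measures that it will be answered only by descriptive arm differences with ward-level 95% intervals (4 against 4 wards, t with 6 degrees of freedom) and no test, or delete it and align the matching aim in Inclusion and Exclusion Criteria.
2. **Feasibility reporting.** Report recruitment counts, dropout and missing data by arm and ward. Check the dropout and missing-data limits within each arm as well as overall; their denominators (people who consented, responses due) can be split by arm. Describe any arm gap in recruitment without a fixed trigger. Apply the participation threshold by arm only if arm-level denominators, such as people eligible or approached, are available.
3. **Wording.** In Study Design, replace not applicable with: not possible; recruitment by arm will be compared.

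The cost is slightly more analysis of data whose ward and arm are known by design, plus three short text changes. No new data collection is needed for the by-arm and by-ward tables. The drawback is that the estimates will be imprecise and must be labelled descriptive. Results are due in 2026, so the commitment should be recorded before the arms are compared.

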## Results

The intervention was launched as planned in July 2024 and is being implemented over a period of 12 months in 8 general ICUs. Data collection is staggered and target group–specific as follows:

Health care professionals: the baseline survey (*t*_0_) was completed in the first 6 weeks of the intervention. A total of 177 participants completed the baseline questionnaire. The follow-up survey (*t*_1_) is scheduled for the end of the intervention period.Relatives: The baseline survey (*t*_0_) is completed during the patient’s ICU stay. A follow-up survey (*t*_1_) is conducted 4 months after *t*_0_ to capture delayed psychosocial burden and changes over time. Recruitment for *t*_0_ took place continuously over 8 months and has been completed. A total of 82 fully completed *t*_0_ questionnaires are available. Eleven *t*_1_ responses have been received to date.Patients: the survey is conducted once (*t*_1_), 4 months after consent and inpatient stay. In May 2025, 72 consents to participate have been obtained and 6 questionnaires have already been completed and returned.

Parallel to the quantitative data collection, the qualitative accompanying research was conducted during the fourth month of the intervention phase. All planned interviews—with the study therapists and a total of 22 health care professionals from the participating wards—were completed and are currently being analyzed. Discussions were also held with patients and relatives on their perception of the study recruitment. In addition, data were collected on which toolbox measures were actually used and which barriers prevented their use. The weekly study therapist documentation on intervention implementation is ongoing. These process indicators demonstrate that recruitment and intervention delivery are feasible within the planned timeline and will provide the empirical basis for assessing the predefined feasibility criteria.

Data collection took place through June 2025. The initial study results are scheduled to be published in 2026, following the completion of data analysis.

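### Randomising the wards first does not make participant-level concealment inapplicable; it opens recruitment of patients and relatives to bias, and the protocol should say so

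*Protocol article*

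**What the plan says.** The Study Design section describes 8 ICUs chosen in advance and allocated "in a 1:1 ratio at the cluster level (ICU"), which implies 4 wards per arm. It then makes two statements on concealment. The first is "Allocation was concealed at the cluster level through the use of a centralized, computer-based randomization procedure". The second is that, because the ICUs were randomised before participants were included, "allocation concealment at the individual participant level was not applicable".

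The section on blinding and contamination says who knew the arm: "The project management, ward management, and the study therapist were informed about the group assignment". It adds that, because the psychologist works visibly within the team, "group assignment can still be inferred based on the care structure". Patients and relatives are told neither their arm nor what the intervention contains.

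The Overview under Pilot Effectiveness Evaluation gives the timing: "Relatives and patients are recruited during the" patient's time on the ICU. Relatives have a baseline survey (t0) in that period. Patients are surveyed only once, at t1, 4 months after ICU discharge. The Results section reports a July 2024 start for the intervention and says that recruitment of relatives for t0 "took place continuously over 8 months and has been completed".

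**The concern.** Concealment at allocation protects against choosing units in the light of the arm they will receive. In a cluster trial there are two such choices: which clusters enter, and which individuals within them are identified, approached and consented. If individuals are enrolled after allocation, the second choice is open to anyone who knows the arm. The protocol takes this order of events as the reason why the question does not arise, when it is the reason why it does.

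The primary research question asks whether a pragmatic RCT is feasible in terms that include recruitment and randomization, and recruitability is the first listed objective. A pilot that marks recruitment bias as inapplicable leaves part of that question unexamined. The last secondary question, on initial evidence of benefit for safety climate and well-being, rests on a comparison that selective enrolment could distort.

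**Working it through.** The protocol gives no figure on this point, so the check sets its statements side by side.

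1. **Order of events.** The wards were randomised before any participant was included (Study Design). The intervention started in July 2024 (Results), and recruitment and baseline data collection began in the same month (Abstract). Patients and relatives were therefore enrolled on wards already allocated, and relatives' recruitment continued for 8 months.

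2. **What cluster-level concealment protects.** All 8 wards were fixed beforehand. Concealing the sequence prevents steering a given ward into a given arm. It does not affect which patients and relatives are later approached.

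3. **Who could know the arm during recruitment.** Project management, ward management and the therapist were told, and other ward staff could infer it. The article does not say which role identified, approached or consented patients and relatives. It therefore neither shows that recruiters knew the arm nor that they did not.

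4. **What the masking covers.** Withholding the arm from patients and relatives limits self-selection and reporting bias on their side. It does not limit selection by a recruiter. The remaining measures in that section concern contamination between wards.

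5. **Whether selection could be detected.**
   - Patients: no outcome is measured at enrolment. Sociodemographic and ICU-stay data are collected, so a partial comparison by arm is possible, but distress at enrolment is not available.
   - Relatives: t0 exists, but on intervention wards it was taken with the intervention already running. A difference at t0 could reflect selection or an early effect.
   - Participation rates: the section on target participation rates relates them to the planned numbers, not to those eligible or approached.

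6. **What the reported counts can tell.** Against the planned numbers:
   - relatives at t0: 82/125 = 65.6%
   - patient consents in May 2025: 72/125 = 57.6%
   - health care professionals at t0: 177/250 = 70.8%

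   These are not split by arm and are not shares of those eligible. They neither show nor exclude selective enrolment.

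Health care professionals also enter after randomisation, with t0 within 6 weeks of the intervention's start, and can infer their arm. The same caveat applies to them.

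**The case against.** The strongest reply is that the protocol is candid. It limits its claim to the cluster level and at once disclaims the individual level. A reader might infer that the trial presents its participants as enrolled under concealment, but the text does not say so. This part of the reply stands: the fault lies in the reason given, not in a false claim of protection.

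A second reply is that the recruiting roles are not named, and an article may leave them to the full protocol. This also stands. A reader might infer that ward management or the therapist picked participants knowing the arm. The documents give neither of them that task, and the silence is not itself an error. But no detail about recruiters could make the stated inference correct. Blinded recruiters would be a safeguard to report, not a reason why concealment does not apply.

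A third reply is that little depends on it here. Analyses are primarily descriptive, no hypothesis tests are planned, and the progression criteria use participation, dropout and missing data, not differences between arms. That limits the consequence. It does not remove it, because recruitment and randomization belong to the primary question and the question on initial evidence remains.

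A reader might also want to size the bias, from the share of admissions enrolled or from a supposed loss of the most distressed patients in one arm. The documents give no admission numbers, only adults able to consent are eligible, and nothing points to one-sided selection. Any such figure would reflect its assumptions and not this trial.

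**Conclusion.** The rationale is wrong as stated and should be corrected. Enrolment took place after allocation, on wards where the arm was known to some staff and open to inference by others, so recruitment bias is not excluded. Whether it occurred, and how large it would be, cannot be determined from the documents.

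The conclusion rests on the protocol's own account of the order of events and of who knew the arm; it needs no assumption about who recruited. The importance is moderate. No confirmatory result is at risk, but the pilot's answer on recruitment and randomization is incomplete without this point, and any between-arm reading of well-being needs the caveat.

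**What to change.** - **Correct the sentence.** Replace it with: participants were identified and consented after allocation on wards where the arm was known or could be inferred, so recruitment bias is not excluded.
- **Query the sites.** Ask each site which role approached patients and relatives, and whether that role knew the arm.
- **Report by arm and ward.** Give consents and the available participant characteristics for each, noting that patients have no baseline outcome and that relatives' t0 followed the start of the intervention.
- **Use the result.** Treat it as part of the feasibility question on recruitment and randomization, and read any between-arm initial evidence with this caveat.

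The cost is one change of wording, a short retrospective query and some extra tabulation. The query is open to recall error because relatives' recruitment has ended, and the stated risk-of-bias position becomes weaker. A fixed rule for whom to approach in the definitive trial would be sensible advice, but it is not a correction to this plan.
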